### Sample size calculation

A sample size calculation has been performed for a multiple linear regression analysis with ten candidate predictor domains: marital status (single, married, divorced, or widowed), age (in years), physical impairment (Karnofsky Performance Status), sex (male/female), depression (PHQ-8), anxiety (GAD-7), social support (SUCE−4), health-related quality of life (EORTC QLQ-C30 and EORTC QLQ-BN20), time since diagnosis (in days) and tumor location (brainstem, frontal, parietal, cerebellum, temporal, occipital, basal ganglia, or spinal). An exploratory sample size calculation was conducted for the planned multiple linear regression analysis, including approximately 20 regression parameters, accounting for the use of dummy coding for categorical variables with more than two levels. Based on a medium effect size assumption (f^2^ = 0.15; corresponding to R^2^ ≈ 0.13), an alpha level of 0.05, and a desired statistical power of 0.80, the required sample size was estimated at 157 participants using G*Power. This calculation should be interpreted as exploratory, particularly given the uncertainty regarding the magnitude of the expected effects and the possibility that effects may be smaller than anticipated. Therefore, all analyses will report confidence intervals and effect size estimates alongside significance tests to allow for an informed interpretation of the findings, irrespective of whether medium-sized effects are observed. To account for an anticipated attrition and data loss rate of approximately 15% (e.g., due to incomplete questionnaires, missing covariate data, or exclusions during data cleaning), the planned recruitment target was increased from 157 to 180 participants.

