#### Statistical analyses

Associations between suicidality and candidate predictors will be examined using regression models appropriate to the distribution of the SSEV outcome, defined as the continuous 6-item SSEV composite score assessing suicidal ideation during the past four weeks. Depending on distributional properties, linear regression models will be used for approximately continuous and symmetric outcomes, while generalized models will be considered in case of marked skewness or zero inflation. All assumptions (including linearity, homoscedasticity, and distribution of residuals) will be assessed and reported where applicable. Prior to multivariable modeling, descriptive statistics and bivariate correlations (Pearson or Spearman, depending on scale properties and distribution) will be computed to describe the data structure. These analyses are purely exploratory and will not be used for variable selection. Multicollinearity will be assessed using variance inflation factors (VIF).

As secondary and sensitivity analyses, additional models will be fitted using (a) a dichotomized suicidal ideation outcome (presence vs. absence of suicidal ideation, defined as a 6-item SSEV score ≥ 1) and (b) lifetime suicide attempts assessed by the dedicated dichotomous SSEV item. These analyses will include the same set of predictors and are intended to assess the robustness of findings across alternative operationalizations of suicidality. All analyses are considered exploratory and hypothesis-generating and are not intended to establish causal relationships.

Given the exploratory nature of the study, all prespecified candidate predictors will be entered simultaneously into a multivariable model without prior univariable screening. To reduce overfitting and improve the stability of estimates in the presence of a relatively high number of predictors, penalized regression (ridge regression with tuning via cross-validation) will be applied. Model performance will be internally validated using bootstrap resampling (e.g., 5,000 resamples) to estimate and correct for optimism in performance metrics. Regression coefficients with 95% confidence intervals will be reported, along with model performance measures such as R^2^ and root mean squared error (RMSE) for the continuous outcome.

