## Perspective

This multicenter observational study with a single cross-sectional assessment will estimate the past-4-week frequency and severity of suicidality [28] and examine cross-sectional associations with demographic, clinical, and tumor characteristics in adults with isocitrate dehydrogenase (IDH) wild-type glioblastoma enrolled between initial diagnosis and first recurrence. Depressive and anxiety symptoms are common in glioblastoma. They are associated with shorter overall survival and poorer health-related quality of life in meta-analytic evidence, whereas suicidality in brain tumor populations appears elevated yet remains incompletely characterized beyond registry-based endpoints. However, the literature is dominated by retrospective registry analyses and small single-center cohorts with variable definitions and observation windows for suicidality, often without standardized assessment of suicidal ideation and attempts. In particular, prior datasets often lack granular neuro-oncologic and treatment variables (e.g., functional status, corticosteroid exposure, antiseizure medication, extent of resection, and molecular markers) alongside standardized patient-reported outcomes, limiting confounder adjustment and interpretability.

The primary objective is to model cross-sectional associations between suicidality (SSEV) and depressive symptoms (PHQ-8), anxiety symptoms (GAD-7), and prespecified demographic, clinical, and tumor characteristics. As secondary objectives, the study aims to characterize the distribution of depressive and anxiety symptom severity and to explore how suicidality and overall symptom burden relate to tumor location, functional status as measured by the Karnofsky Performance Score, and perceived social support (SUCE−4) [29].

To achieve these goals, the protocol combines validated patient-reported outcome measures with standardized neurological examination and structured abstraction of treatment and imaging variables across centers.

The study is designed to minimize patient burden by integrating all procedures into a single outpatient visit, while ensuring that data are collected in a standardized manner across multiple centers using a standardized case report form and training before delegation.

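### Ridge on reference-coded dummies makes the reported tumor-location and marital-status differences depend on the reference level, and no factor-level assessment is among the outputs described

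*Protocol article*

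**What the plan says.** The Sample size calculation section lists ten predictor domains. Two are multi-level: tumor location with eight categories and marital status with four. The model is described as "including approximately 20 regression parameters, accounting for the use of dummy coding for categorical variables with more than two levels". The same section promises that "all analyses will report confidence intervals and effect size estimates alongside significance tests", without saying whether these tests concern single coefficients or whole factors.

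The Statistical analyses section enters all predictors at once, applies ridge regression tuned by cross-validation, and states: "Regression coefficients with 95% confidence intervals will be reported". Performance measures such as R² and RMSE are to accompany them. The same predictor set is used again for dichotomized ideation and for lifetime suicide attempts. All analyses are declared exploratory.

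The Perspective section gives as a secondary objective to "explore how suicidality and overall symptom burden relate to tumor location". The article names no reference level, no factor coding for the penalized fit and no joint test.

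**The concern.** The location objective concerns a factor, but the only predictor-level output described is a set of coefficients, each comparing one level with a reference. Two problems follow.

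First, in an unpenalized model the reference is harmless, because any difference between two levels is the same whichever level is omitted. Under ridge this is no longer true: the penalty pulls every dummy coefficient to zero, which means towards the reference level. Two analysts with the same data and the same penalty would publish different location effects.

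Second, location offers seven intervals and marital status three. A reader who takes any interval excluding zero as evidence for the factor has several chances of a false lead. The Perspective section expects candidate correlates from this dataset to inform screening pathways, so a lobe singled out by coding or by repeated looks could be carried forward.

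**Working it through.** **1. The plan's own figure.** Inputs from the Sample size calculation section: f² = 0.15, "an alpha level of 0.05, and a desired statistical power of 0.80", about 20 parameters. R² = 0.15/1.15 = 0.130. For the overall F test with u = 20, v = N − 21 and noncentrality 0.15·N, the smallest N with power of at least 0.80 is 157 (power 0.803; u = 19 gives 153, u = 21 gives 160). The figure reproduces. It is the power for the whole model, not for any one factor. Location contributes 8 − 1 = 7 parameters and marital status 4 − 1 = 3, so 10 of about 20. With 15% loss from 180, N = 180 × 0.85 = 153.

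**2. Why the reference matters under ridge.** Let d be the difference between levels A and B, with penalty λ times the sum of squared coefficients on unstandardized dummies.
- Reference is a third level: d can be carried as +d/2 and −d/2, at a cost of λ(d²/4 + d²/4) = λd²/2.
- Reference is A or B: one coefficient must carry all of d, at a cost of at least λd².

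The same difference therefore costs at least twice as much when one of its two levels is the reference. This needs no assumption about level frequencies.

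**3. Size in one simulated dataset** (N = 157, assumed skewed location mix), frontal-minus-temporal difference over all eight references:

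| Penalty | Lowest | Highest |
|---|---|---|
| none | 1.177 | 1.177 |
| λ = 10 | 0.57 | 0.91 |
| λ = 30 | 0.32 | 0.63 |
| λ = 100 | 0.13 | 0.31 |

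A second simulated dataset showed the same pattern: 0.328 under every reference without penalty, 0.15-0.27 at λ = 10 and 0.04-0.11 at λ = 100.

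With the penalty tuned afresh by 10-fold cross-validation (500 runs, five location levels, true temporal-minus-frontal difference 0.5 SD), mean estimates under four references were 0.181, 0.243, 0.293 and 0.293. The shortfall from 0.5 is mostly intended shrinkage; the spread from 0.18 to 0.29 is due to the reference.

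**4. Any-dummy false positives with no location or marital effect, unpenalized linear fits.** Independent tests would give 1 − 0.95⁷ = 30.2% for location and 1 − 0.95³ = 14.3% for marital status. The dummies share a reference, so simulation is needed. The article gives no level frequencies; all mixes are assumptions.

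| Setting | Any location dummy |
|---|---|
| N = 157, equal shares | 23% |
| N = 157, skewed; reference frontal / parietal / occipital | 27% / 28% / 23% |
| N = 157, skewed; reference brainstem / spinal | 16% / 14% |
| N = 153, two skewed eight-level mixes; reference frontal or occipital | 21-29% |
| N = 153, only five levels occurring | 11-17% |

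For marital status the rate was 12-15%. A small run of ridge with bootstrap percentile intervals (250 runs) gave 35-43% for location and 14-23% for marital status. The article does not say how intervals around ridge coefficients will be formed, so these figures are only indicative.

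**5. Joint tests on the same kind of data.** Partial F tests (7 and 3 df) rejected in 4.7-5.6% of runs at N = 157 with a normal outcome and do not depend on the reference. With an outcome that is 78.5% zeros (100 − 21.5, borrowing the share with suicidal thoughts in the German cohort cited in the Introduction), the linear-model 7-df test rejected in 7.4-8.9%. In the five-level mix the 4-df test rejected in 4.6-5.1%.

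Power of the 7-df location test at N = 157 with 20 parameters: 0.19, 0.47 and 0.82 at partial f² = 0.02, 0.05 and 0.10. For the 3-df marital test: 0.28, 0.63 and 0.92.

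**The case against.** The strongest reply is that much of this is silence in a condensed article. The list of outputs is open-ended, the promised significance tests are of unspecified type, and a joint test or a reference level may sit in an analysis plan that is not shown. A reader might infer that the location question will go untested, or will be judged from single dummies alone. The documents do not support either inference. The objective is worded as exploring how suicidality relates to location, which does not commit the study to a yes/no test.

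A reader might also take a figure in the twenties of percent as the plan's error rate. That does not stand either. No rule in the article declares a correlate when one interval excludes zero. The rate varies with the reference and with frequencies the article does not give, it comes from unpenalized fits, and it is lower for marital status. The article calls all analyses hypothesis-generating and says correlates need validation in independent cohorts. The MRI section also promises rules for multilobar and multifocal disease, so the final location coding may differ from eight exclusive levels.

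A joint test has costs too. Its power is limited for small effects, and letting it gate every level estimate would be hard to defend in an exploratory study.

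These points remove any claim of a missing test or a breached error rate. They do not touch the reference dependence, which follows from two things the article does state: dummy coding and ridge.

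**Conclusion.** The point holds in limited form. Ridge on reference-coded dummies gives location and marital-status differences that change with an arbitrary choice, by roughly a factor of 1.6 to 2 in the examples (0.293/0.181 = 1.6 with cross-validated tuning; 0.63/0.32 = 2.0 at λ = 30). The dependence itself is algebraic; its size rests on simulated data and assumed mixes.

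No factor-level assessment is among the outputs described, although location is a secondary objective. Reading single dummies as evidence for a factor would give false positives in about 14-29% of studies for eight-level location and 12-15% for marital status, in unpenalized linear fits at N of 153-157. This describes a possible misreading and not a rule the plan adopts. The correction is cheap and worth making.

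**What to change.** Amend the Statistical analyses section as follows.

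- **Ridge coding.** For tumor location and marital status, enter all level indicators with an unpenalized intercept and a common penalty within the factor, or use an equivalent reference-invariant group penalty. Do not use k − 1 reference-coded columns. Ordinary sum-to-zero coding with k − 1 columns does not solve the problem: in the second dataset above the difference still ranged from 0.27 to 0.33 at λ = 10, depending on which level was dropped.
- **Joint test.** For each of the two factors, report one joint test from the unpenalized model of the family chosen for the outcome, pooled over imputations, with up to 7 df for location and 3 df for marital status after merging levels too sparse to estimate. Taking the test from the chosen family matters because the linear-model F test was somewhat liberal with a mostly-zero outcome.
- **Reporting.** Show the joint result beside the level-wise estimates and label the latter descriptive. The joint result need not gate them.

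Cost: a few sentences and two extra test statistics per model, with no new data or patients. The downside is slightly more analysis work and a joint location test with limited power for small effects (about 0.47 at partial f² = 0.05), so a non-significant result should not be read as absence of a location effect.

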## Perspective

This multicenter observational study with a single cross-sectional assessment will estimate the past-4-week frequency and severity of suicidality [28] and examine cross-sectional associations with demographic, clinical, and tumor characteristics in adults with isocitrate dehydrogenase (IDH) wild-type glioblastoma enrolled between initial diagnosis and first recurrence. Depressive and anxiety symptoms are common in glioblastoma. They are associated with shorter overall survival and poorer health-related quality of life in meta-analytic evidence, whereas suicidality in brain tumor populations appears elevated yet remains incompletely characterized beyond registry-based endpoints. However, the literature is dominated by retrospective registry analyses and small single-center cohorts with variable definitions and observation windows for suicidality, often without standardized assessment of suicidal ideation and attempts. In particular, prior datasets often lack granular neuro-oncologic and treatment variables (e.g., functional status, corticosteroid exposure, antiseizure medication, extent of resection, and molecular markers) alongside standardized patient-reported outcomes, limiting confounder adjustment and interpretability.

The primary objective is to model cross-sectional associations between suicidality (SSEV) and depressive symptoms (PHQ-8), anxiety symptoms (GAD-7), and prespecified demographic, clinical, and tumor characteristics. As secondary objectives, the study aims to characterize the distribution of depressive and anxiety symptom severity and to explore how suicidality and overall symptom burden relate to tumor location, functional status as measured by the Karnofsky Performance Score, and perceived social support (SUCE−4) [29].

To achieve these goals, the protocol combines validated patient-reported outcome measures with standardized neurological examination and structured abstraction of treatment and imaging variables across centers.

The study is designed to minimize patient burden by integrating all procedures into a single outpatient visit, while ensuring that data are collected in a standardized manner across multiple centers using a standardized case report form and training before delegation.

From an operational standpoint, the study addresses the practical challenges of recruitment, cognitive impairments, language limitations, and data completeness. Trained staff oversee standardized questionnaire completion without influencing responses to ensure high-quality, reliable data. The study design also allows for the exploration of psychosocial variables underrepresented in routine neuro-oncological practice, such as perceived social support.

The resulting multicenter dataset will support empirically grounded hypotheses and candidate correlates of suicidality that may inform pragmatic screening pathways and require validation in independent prospective cohorts. If replicated, the identified associations can inform the design of targeted, testable psycho-oncological interventions and referral algorithms, which will require prospective interventional studies to demonstrate improvements in patient-centered psychosocial outcomes.

## Conclusions

This multicenter cross-sectional observational study aims to explore potential clinical, demographic, and psychological correlates of suicidality in patients with glioblastoma treated in German neuro-oncology centers. By identifying factors associated with suicidality and related outcomes, the study seeks to generate hypotheses for future research and to improve the understanding of suicidality in this patient population.

Given the exploratory design, the findings are not intended to establish causal relationships but may help inform the development of future prospective studies and support the identification of patients at increased psychological risk. Suicidality and related psychological symptoms remain highly relevant for patient quality of life in neuro-oncology and warrant further systematic investigation.

## Data Availability

No datasets were generated or analysed during the current study.
